### Acceptability of the intervention

Semi structured interview schedules will be designed and used to gather feedback on the acceptability of the interventions from group A and B participants during the 24 week research assessment. This part of the study will capture the patient and carer voice and experience of the rehabilitation interventions relative to perceived needs and priorities. In addition, service providers, MDT members, care assistants and a selection of commissioners will be asked for their views about the interventions, to identify strengths and weaknesses, barriers and facilitators to the wider use of the interventions.

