## Design/Methods

### Design

A pragmatic three parallel group randomised controlled trial. People with Parkinson's in group A will be assessed and managed by a specialist MDT according to a care plan that is agreed amongst the professionals and with the patient and carer. Group B will additionally receive ongoing support for four months from a trained care assistant. Group C will receive normal care (no coordinated MDT care planning or ongoing support). Follow up will be for six months to determine the impact and relative cost-effectiveness of the two interventions. Qualitative interviews will be undertaken with providers (MDT members, care assistants), service commissioners, and patients and carers in groups A and B, to gain feedback about the acceptability of the interventions. The CONSORT diagram [42] summarises the design (Figure 1).

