### Outcome measures

Participants in all groups will be assessed in their homes by a research nurse, according to the schedule used in the day hospital trial, at weeks 6 (after the rehabilitation intervention), 24 (four months after the end rehabilitation, coinciding with the end ongoing support for Group B), and 36 (for final follow up). Validated instruments which reflect the needs of participants (e.g. functional outcomes, quality of life) and service commissioners (e.g. service use), and which have been found sensitive in previous rehabilitation studies undertaken by the research team [10-13] have been selected to measure outcomes (Table 1).

**Table 1 T1:** Trial outcome measures and instruments: baseline, 6, 24 and 36 weeks

Participant	Outcome measure	Instrument
Person with Parkinson's	Parkinson's disability/general activities	Self Assessment Parkinson's Disease Disability Scale [46] (PRIMARY OUTCOME)
	
	Parkinson's specific	Parkinson's Disease Questionnaire [47]
		
		Non Motor Symptom Questionnaire [48]
	
	Mobility	Posture and gait items from the Unified Parkinson's Disease Rating Scale [49]
		
		Timed up and go [50]
	
	Falls	Self report
	
	Speech	Single speech item from the Unified Parkinson's Disease Rating Scale [49]
		
		Abridged Emerson and Enderby Screening Assessment Rating Scale [51]
		
		Frenchay Dysarthria Summary [52]
		
		Speech self report questionnaire [10-12]
	
	Pain	Visual analogue scale [53]
	
	Generic health related quality of life/QALYs	Euro Qol 5D, with utility index for calculation of quality adjusted life years (QALYs) [54]
	
	Self efficacy	Self efficacy scale [55]
	
	Health and social care utilisation	Customised proforma and patient records

Live-in carer	Carer strain	Modified caregiver strain index [56] (PRIMARY OUTCOME)
	
	General health	General health questionnaire - 12 [57]

Both	Activities of daily living	Barthel ADL index [58]
	
	Social activities	Frenchay Activities index [59]
	
	Psychological wellbeing	Hospital Anxiety and Depression Scale [60]
		
		Yale single item depression screening tool [61]
	
	Generic health related quality of life	Short form - 36 Health Survey [62]

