The instrument battery was developed and piloted in collaboration with patient and carer representatives. It takes about one hour to complete, and was not been found too onerous. Research nurses will assist patients with completion of questionnaires. Carers will be asked to self complete the questionnaires that apply to them. All questionnaires will be checked for completeness before the research nurse leaves the participant's home. Data will be entered by the research nurse shortly after collection, and any queries referred back to the participant by telephone. A further check on data (completeness and entry) will be undertaken by the research manager when forms are returned to the office by the research nurse, and missing items or other issues will be resolved. Patient and carer outcomes will be analysed separately.

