### Blinding

The research administrator will not disclose group allocation to the research nurses who undertake assessments, and participants will be asked not to discuss aspects of the trial and treatments with them. However, it is recognised that blinding of the research nurses may be compromised in trials of this nature. As a check on blinding, research nurses will be asked to guess participants' groups at the end of the trial. For data analysis, the group identifiers will not be disclosed to the statistician.

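### Acceptability interviews for Groups A and B only, set inside the week-24 nurse assessment, are likely to show blinded assessors who is treated and to spoil the end-of-trial blinding check

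*Protocol article*

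**What the plan says.** All references are to the protocol article.

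- **Outcome measures.** "Participants in all groups will be assessed in their homes by a research nurse", at weeks 6, 24 and 36. On the patient instruments, "Research nurses will assist patients with completion of questionnaires"; carers fill in their own.
- **Blinding.** The administrator "will not disclose group allocation to the research nurses who undertake assessments", and participants are asked to keep quiet about their treatment in front of the nurses. The section concedes in general terms that nurse blinding may not hold. As the check, "research nurses will be asked to guess" each participant's group once the trial ends.
- **Acceptability of the intervention.** Semi-structured interviews will "gather feedback on the acceptability of the interventions from group A and B participants during the 24 week research assessment".
- **Design.** This confirms who is interviewed: providers, "service commissioners, and patients and carers in groups A and B, to gain feedback about the acceptability of the interventions". Group C is not included.

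**The concern.** Two adjacent sections pull against each other. One keeps the allocation from the assessing nurse and asks participants not to talk about treatment. The next places a conversation about treatment experience, for the treated arms only, inside that nurse's visit. Whether the interview takes place is itself information about allocation.

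Weeks 24 and 36 carry the pairwise comparisons of A and B with usual care (Statistical methods). If assessors know who is treated when they score, detection bias can enter those comparisons. Separately, a blinding check made only after the disclosure says nothing about the period before it, so readers of the results could not judge how well the assessors had been blinded.

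**Working it through.** The plan gives no figure on this point to reproduce, and no sample-size or power figure depends on it. The check is a reading of the sections together, plus one short calculation.

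**1. Can the nurse learn the arm?** The article does not name the interviewer.
- If the nurse interviews, she has to know which participants are in A or B.
- If someone else interviews at the same visit, the nurse can infer A/B from that person's presence unless it is hidden from her. The article describes no separate contact, no concealment and no matching interview for Group C.
- A versus B is disclosed only if the interview touches on care-assistant support, which Group B alone receives.

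**2. Which time points are exposed?**

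| Assessment | Exposed to the interview? | Condition |
|---|---|---|
| Week 6 | No | It precedes the interviews |
| Week 24 | Possibly | The interview comes before scoring, or the nurse knows of it beforehand; the order is not stated |
| Week 36 | Possibly | The same nurse returns, or the information is shared; no new assessor is required |

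**3. Which outcomes are exposed?** Taking Table 1 with the statements on who completes what:
- Most: items that the visiting nurse would rate or administer (UPDRS posture, gait and speech items, timed up and go, speech ratings). All are secondary.
- Less: the patient primary outcome. It is a self-assessment by patients who have been told their group (Registration and randomisation), so the nurse's influence is limited to help with completion.
- Least: carer strain, which carers complete themselves.

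**4. What would the end-of-trial guess show?** Inputs: 270 patients, 90 per group (Sample size calculations). Assume for illustration that all are retained.
- No knowledge: expected correct share = 1/3 = 33%.
- A/B versus C known for everyone: all 90 in C are correct, and half of the 180 in A and B by chance, which is 90. Share = (90 + 90)/270 = 2/3 = 67%.
- The article does not say that every A/B participant is interviewed. Let *p* be the proportion who are, with the nurse calling everyone else C. Correct guesses = 90 + ½ × 180 × *p*, so the share is (1 + *p*)/3: 33% at *p* = 0, 50% at *p* = 0.5 and 67% at *p* = 1.

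A result anywhere in this range could come from the interview schedule alone. A nurse fully blind up to the week-24 visit and a nurse who already knew A/B versus C at week 6 would, with *p* = 1, give the same 67%. The check cannot tell them apart.

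**The case against.** The strongest reply is that the mechanism is inferred. The article names neither the interviewer nor the point in the visit at which the interview falls. The team includes a qualitative researcher (Management and governance), and a journal article may leave such details to the full protocol. If the interview follows the outcome battery and the nurse has no warning, week-24 scores are already recorded. Nothing says that the same nurse returns at week 36. This stands, and it is why the exposure is conditional at both time points. It does not remove the conflict, because the article does fix the timing, and fixes it within the visit of an assessor who is meant to be blind.

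A second reply is that the article already concedes that blinding may fail, and that other routes to disclosure exist: self-reported service use is collected at each assessment (Economic evaluation) and might reveal therapy contacts. This also stands. Moving the interviews will not by itself secure blinding. But a general concession is no reason to schedule a disclosure that can be avoided.

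A third reply is that the patient primary outcome comes from patients who know their group, so assessor blinding protects it only in part. That is correct, and it places the main risk with the nurse-rated secondary outcomes.

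**Conclusion.** The conflict is real and worth correcting before week-24 visits take place, as a cheap improvement. As written, the interviews are likely to reveal A/B versus C to the assessing nurse, under the conditions set out for weeks 24 and 36. The risk falls mainly on nurse-rated or nurse-administered secondary outcomes. The blinding check cannot show whether nurses were blind at week 6 or when scoring week 24. The 67% against 33% rests on equal allocation, full retention, all A/B participants being interviewed, and no knowledge of A versus B.

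A reader might infer more, namely that every participant becomes identifiable from week 24 and that both later time points are certainly biased. The article does not support that. It does not say that all A/B participants are interviewed, and participants can withdraw or miss a visit, so a missing interview does not prove Group C. The order within the visit and the week-36 assessor are also left open.

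Nor can the bias be given a size. One could posit a 0.25-point shift in assisted scoring, which is 0.25/1.25 = 20% of the target difference in disability, but nothing in the article supports that value or any other.

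**What to change.** 1. Take the acceptability interviews out of the research nurse's week-24 assessment. Have the qualitative researcher hold them in a separate contact once that participant's week-24 outcomes are recorded. Do not tell the nurses who is interviewed, and ask participants not to mention it to them. Holding the interviews after the week-36 assessment is an alternative.
2. Have the nurse record an allocation guess at the end of each assessment (weeks 6, 24 and 36), and report the three sets separately.

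**Cost.** The first option needs one extra contact per interviewed A/B participant, at most 180 if all are interviewed. Telephone contact may be hard for those with speech problems, so some would need a visit. The alternative lengthens recall by 36 − 24 = 12 weeks; for Group A, whose six-week programme ends at about week 6, the gap grows from about 18 to about 30 weeks. The repeated guess adds one item per visit. No sample-size or analysis figure changes.

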### Sample size calculations

Patient sample size calculations were based on detecting clinically meaningful differences in the primary patient outcome measure. Carer sample sizes reflect the findings of our previous work that suggest that 79% of people with Parkinson's have a carer [10].

We will recruit 270 people with Parkinson's over a 12 month period across the three areas, 90 of whom will be randomly allocated to each of the three groups. This calculation is based on the numbers of people with Parkinson's needed to detect differences between groups in patient primary outcome measure score.

Assuming a similar level of variation in Self Assessment Parkinson's Disease Disability Scale [46] to the day hospital trial [11], in order to detect a difference in the disability score of 1.25 (assuming SD = 2.5, size = 5%, power = 80% and a 2 sided test), 64 subjects with Parkinson's disease are needed in each of the three groups.

Assuming a similar level of variation in Carer Strain Index [56] to the day hospital trial [11], in order to detect a difference in the Carer Strain Index of 0.535 (assuming SD = 1.07, size = 5%, power = 80% and a 2 sided test), 64 carers are needed in each of the three groups. In the previous study, 79% of community dwelling people with Parkinson's had a live-in carer [10]. Thus, if we have 64 carers per group, this will necessitate 246 [(64*3)/0.79 = 243.04] Parkinson's subjects, i.e 82 per group.

In the previous day hospital trial the loss to follow-up/non completion/missing data rate between recruitment and six month assessments was 26%. However, in this trial, participants attended the day hospital for treatment (six visits) and research assessments (four visits), and difficulties with transport and inter-current illness accounted for missing data and drop-out. We expect less attrition in the SPIRiTT trial because participants will receive both treatment and the research assessments in their own homes, at times convenient to them.

If we allow for 10% loss to follow up/non completion/missing data rates for people with Parkinson's, then 243.04/.90 = 270.03 patients are required = 90 per group. With 90 patients per group, we expect to recruit 71 carers per group. These group sizes will also ensure that the samples for patients and carers will both remain above the critical values of 64 if there were a loss of 5% of carers (and associated patients) and an independent loss of 5% of people with Parkinson's. Intention to treat analysis will be used.

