### Recruitment

People with Parkinson's disease will be identified by a variety of means including: hospital clinics; general practitioners (GPs); Parkinson's UK contacts; PNS, community-based therapists; word of mouth. Research nurses from the Primary Care Research Network (PCRN) and the Dementia's and Neurodegenerative Diseases Research Network (DeNDRoN) will assist with the identification of people with Parkinson's through general practices and specialist Parkinson's hospital clinics respectively. Any interested person with Parkinson's will be given an information leaflet. Separate information will be provided for live-in carers (family, friends, paid carers living in the same household), where appropriate. People with Parkinson's and live-in carers will volunteer separately to take part in the study by contacting the research team, who will undertake an initial eligibility screen. This screening will include asking the patient to confirm that a doctor has told them that they have Parkinson's disease. Volunteers who meet the inclusion criteria (see below) will be sent full information about the trial, and a consent form, and an appointment will be made for a research nurse to make a home visit to collect baseline information. If a live-in carer does not want to take part in the research, the person with Parkinson's may still join the trial. However, carers will not be accepted if the person with Parkinson's does not want to participate.

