## Discussion

The SPIRiTT trial is a community based MDT rehabilitation intervention for people with Parkinson's disease and their live-in carers. The intervention is delivered to people in their own homes, so that the costs and effectiveness can be compared with a similar intervention delivered to the same patient group in a day hospital setting. Findings will be compared with another community-based RCT, conducted in England recently that found no significant difference in outcomes or costs of patients receiving rehabilitation in a day hospital rather than in their own homes [66].

We anticipate several problems in the conduct of the trial and will put processes in place to avert or minimise their effect. First, retention of participants, particularly in the control group, may be difficult so we will seek to retain their interest by providing regular newsletters reporting trial progress. Patients randomised to the control group will be offered an MDT assessment and advice on completion of the trial follow up. Second, disruptions to the delivery of the MDT intervention may arise due to bad weather preventing travel, or staff sickness. We expect such interruptions will be minimal and consistent with a pragmatic approach to research on service delivery, and that cover will be available within the team for short term holiday or sickness leave. Third, lack of local NHS resources, due to financial exigencies, could impede the delivery of the intervention according to protocol to the numbers of patients and carers required by the sample size calculations, but we will liaise with local commissioners and providers to try and ensure their support. Fourth, recruiting MDT members and care assistants may be problematical, due to difficulties arranging temporary secondments from local providers, and local labour market conditions. We will address any staffing issues by advertising widely and offering favourable contracts for suitably qualified applicants. Lastly we may encounter difficulties in persuading live-in carers to take part in the research assessments, and we will seek to overcome this by explaining why their participation is important to the findings.

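### The 80% power for carer strain in the pairwise 24- and 36-week comparisons presumes that essentially every live-in carer takes part

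*Protocol article*

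**What the plan says.** All places are in the protocol article.

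- **Sample size calculations, carer target.** For a difference of 0.535 on the Carer Strain Index with SD 1.07, two-sided 5% and 80% power, "64 carers are needed in each of the three groups".
- **Sample size calculations, conversion to patients.** The previous study found that "79% of community dwelling people with Parkinson's had a live-in carer". From this, "this will necessitate 246 [(64*3)/0.79 = 243.04] Parkinson's subjects, i.e 82 per group". Dividing 243.04 by 0.90 for loss gives 270 patients, 90 per group.
- **Sample size calculations, expected yield.** "With 90 patients per group, we expect to recruit 71 carers per group". The next sentence says that patients and carers will both stay above 64 under a 5% loss of carers combined with an independent 5% loss of patients.
- **Recruitment.** Patients and carers volunteer separately. "If a live-in carer does not want to take part in the research", the patient may still be enrolled.
- **Discussion.** Among the anticipated problems: "we may encounter difficulties in persuading live-in carers to take part in the research assessments". The remedy offered is to explain why their participation matters.
- **Statistical methods.** Carer strain is tested at week 6 (A and B together against C) and in all three pairwise comparisons at weeks 24 and 36, using t tests on change from baseline, or Mann-Whitney tests if assumptions fail.

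**The concern.** The 79% describes how many patients have a live-in carer. The calculation uses it as the number of carers who will enrol. Those are the same only if every live-in carer is eligible and consents. The article's recruitment rules allow refusal, and its Discussion expects some, yet no term for refusal enters the chain from 64 to 270.

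Carer strain is one of the two primary outcomes. If fewer carers enrol than assumed, a null result in a pairwise carer comparison would be read against a power of 80% that the comparison did not have.

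**Working it through.** **Inputs from the article:** difference 0.535, SD 1.07, two-sided 5%, 80% power; 79% of patients with a live-in carer; 90 patients per group; 10% loss; equal allocation. **Input not in the article:** carer uptake *p*, the fraction of live-in carers who enrol. It is varied below as an assumption.

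**1. Reproducing the plan's figures.**
- Standardised difference: 0.535 / 1.07 = 0.5. The two-sample t test needs 63.8, so 64 per group; power at 64 is 80.1%.
- Patients before loss: (64 x 3) / 0.79 = 243.04.
- Patients after the loss allowance: 243.04 / 0.90 = 270.04, so 270, or 90 per group.
- Expected carers: 90 x 0.79 = 71.1 per group.

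Every step reproduces, and it does so only with *p* = 1.

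**2. Reserve in the plan.**
- After 10% loss: 71.1 x 0.90 = 63.99.
- Under the 5% plus 5% scenario: 71 x 0.95 x 0.95 = 64.08.
- With one carer fewer at the start: 70 x 0.95 x 0.95 = 63.2.

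The uptake at which exactly 64 carers remain is 64 / (71.1 x (1 - loss)): 100% with 10% loss, 99.7% with the 5% plus 5% scenario, and 90% with no loss at all.

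**3. Pairwise power once uptake enters.** Analysable carers per group = 90 x 0.79 x *p* x 0.90; power from the noncentral t distribution at a standardised difference of 0.5.

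| Assumed uptake | Carers per group | Pairwise power |
|---|---|---|
| 100% | 64.0 | 80% |
| 95% | 60.8 | 78% |
| 90% | 57.6 | 76% |
| 80% | 51.2 | 71% |
| 70% | 44.8 | 65% |

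**4. Higher loss, as a sensitivity case only.** At the previous day hospital trial's 26%: full uptake gives 71.1 x 0.74 = 52.6 carers and 72% power; 80% uptake gives 42.1 and 62%.

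**5. Comparisons not materially affected.**
- Week 6, A+B against C, same standardised difference, 10% loss: 128 against 64 carers at full uptake gives 90%; 102.4 against 51.2 at 80% uptake gives 83%; 96 against 48 at 75% uptake gives 80%.
- Patient disability, 1.25 / 2.5 = 0.5: 90 x 0.90 = 81 per group gives 89%; even 26% loss leaves 66.6 and 82%.

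**The case against.** Several points on the other side stand.

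- **No step is miscalculated.** The fault is an unstated assumption about participation.
- **The assurance of staying above 64 is conditional, and true on its own terms.** A reader might infer that it is simply false. It is not: starting from 71 recruited carers, the described losses leave 64.08. What it does not cover is refusal before recruitment, so the weak part is the starting figure of 71.
- **The loss allowance has a rationale.** A reader might infer that 10% is untenable because the previous trial lost 26%, or that it covers only six months and so misses week 36. The article does not support either reading. It attributes much of the 26% to day hospital attendance and transport, and this trial treats and assesses people at home. The six-month time point belongs to the 26%; the 10% carries no time point. No carer-specific loss rate is given.
- **The shortfall depends on an assumed uptake.** At 95% it is about two percentage points, which is trivial. The Discussion says only that difficulties may arise, and it names a mitigation.
- **Carer strain is not underpowered throughout.** The pooled week 6 comparison keeps 80% or more down to about 75% uptake with 10% loss.

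None of this supplies the missing uptake term. The 64-per-group figure serves the pairwise comparisons, and with the plan's own 10% loss any appreciable refusal takes them below 80%.

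**Conclusion.** The point holds for the pairwise carer strain comparisons at weeks 24 and 36. Their stated 80% power requires essentially full uptake by live-in carers and no more than 10% loss. With 10% loss and uptake between 95% and 70%, power is about 78% to 65%. The uptake range is an assumption, because the article states none; the article's SD of 1.07 and target difference of 0.535 are taken as given.

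A reader might go further and conclude that the trial is underpowered for carer strain generally, or for its primary outcomes as a whole. The document does not support that: the week 6 carer comparison and the patient outcome have enough margin. This is a statement of power that should be corrected, not a reason to redesign the trial.

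**What to change.** 1. In Sample size calculations, say that 71 carers per group and 80% pairwise power presume that every live-in carer takes part and that loss is at most 10%.
2. Report pairwise power for carer strain over a range of uptake, such as the 95% to 70% tabulated above. Show higher loss, up to the previous trial's 26%, only as a sensitivity case.
3. Make clear that the assurance of staying above 64 starts from 71 recruited carers and does not allow for refusal at entry.
4. For the main carer comparisons, use ANCOVA adjusted for baseline in place of t tests on change scores. Baseline carer strain is already collected, and the Economic evaluation section already plans this adjustment for carer strain. It should recover some precision, but the gain cannot be quantified here: it depends on the correlation between baseline and follow-up, which is not stated, and the article does not say whether the SD of 1.07 refers to scores or to changes.

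Cost: wording, one change to the planned carer analysis, and a less favourable stated power for that outcome. No extra recruitment is needed.
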